##### Design

A phase I/II, randomized, single blind study. Subjects with prostate cancer with rising PSA levels who have failed conventional therapy are eligible.

A total of 24 patients will be enrolled into one of two Arms of 12 patients each. Subjects will be randomly assigned (1:1) at entry to one of the two vaccination groups.

Patients in Arm 1 will receive one immunization and 3 booster immunizations over the course of the first 7 weeks of study. Patients in Arm 2 will receive a placebo (either saline or vaccine vehicle only (5% DMSO in normal saline) immunization and 3 placebo booster immunizations, and will switch after week 7 to the vaccination arm, where they will receive one immunization and 3 booster immunizations exactly as for patients in Arm 1.

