#### Biostatistical analysis.

The primary specific aim is to compare the clinical status during the first part of the study (before the cross-over) between the placebo and the vaccine group. As defined in CFR, Phase-I/II studies should address both acute toxicity and activity/efficacy. Accordingly, this comparison will be based on two primary outcomes:

(1) activity: relative change in PSA.

We do not use the term “efficacy” here, because we recognize that change in PSA is not a validated “surrogate” for clinical benefit. The primary manifestations of disease progression in prostate cancer are rising PSA values, new lesions on bone scan, new symptoms of disease, and, less frequently, an increase in measurable tumor mass. Several groups have shown the prognostic significance of post-therapy declines in PSA, leading to an NCI consensus group proposal of a set of guidelines for the use of post-therapy PSA that can be used in phase II trials to identify agents for further testing (Fazzari et al., 2000).

(2) acute toxicity: incidence and severity of an adverse events.

Although the variables will be combined to address the overall clinical status, the power calculations below address each of these aspects independently.

Size of relevant differences: For activity, we would like to have sufficient power to detect a 50% decline in PSA in the treatment group vs. no change in the placebo group. For toxicity, we would like to have sufficient power to detect a 50% incidence of severe adverse events (acute toxicity) vs. a 5% incidence.

Power vs. level: If there should be acute toxicity, we do not want to overlook this (false negative result). A similar argument holds for activity: as long as the treatment with apoptotic LNCaP-DCs is well tolerated, we would rather go on with the next trial, even if we would later find out that apoptotic LNCaP-DCs are not active (false positive result), than to risk delaying the development of an effective treatment (false negative result). Thus, we want to guarantee 90% power for the above differences at the 10% level. If we should see lower acute toxicity in the vaccine group (unlikely) or higher activity in the placebo group (also unlikely), our decision would be the same as if we would see no difference: we would reconsider the use of this vaccination in the treatment of advanced prostate cancer. Given this one-sided decision strategy we will further increase power by using one-sided tests.

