Statistical model: As the form of the relationship between changes in PSA and clinical success is unknown, we will use a Wilcoxon-Mann-Whitney Ranktest to compare activity. For SAEs, the exact Fisher test will be used.

Sample size: To detect any difference with 90% power at the 10% level (one-sided) the WMW test’s chi-square distribution must have a non-centrality parameter of 8.2 under the alternative. By our inclusion criteria, all patients will have had rising PSA levels prior to study entry. Thus, for the power calculation, we assume that PSA continues to remain elevated or to increase over the 9 week study period for at least two-thirds of the patients in the placebo group. If the vaccination should be active, PSA should decrease in two-thirds of the patients in the vaccine group. If we assume that even the largest decline expected in the placebo group does not exceed 50%, then this corresponds to the consensus agreement that a 50% decline should be considered relevant (Bubley et al., 1999; Fazzari et al., 2000). Conservative scenarios of relevant differences in PSA responses between the vaccine and placebo group, yield sample sizes between 9 and 13. From a Bayes'ian perspective, none of these alternative hypotheses is unlikely. Thus, with a sample size of 12 per group we can expect at least 90% power for detecting relevant activity at the 10% level for changes in PSA.

Regarding toxicity, this sample size also guarantees a 90% power to detect an increase in the cumulative incidence of SAEs from 5% in the placebo group to 50% in the vaccine group at the 10% level (or a 80% power at the 5% level). A 40% cumulative incidence could be detected with 80% power at the 10% level (or a 90% power at the 20% level). If no SAEs are seen in the placebo group, three SAEs in the vaccine group yield a p-value of .109 (one-sided, exact). With one SAE in the placebo group, four and five severe adverse events in the vaccine group yield a p-value of .158 and .077, respectively.

This suggests the following conservative stopping rule for the study: After the third SAE in the vaccine group, the study is stopped if no SAEs have occurred in the placebo group until this time. After the fourth SAE in the vaccine group, the study is stopped unless more than one SAE has already occurred in the placebo group.

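### None of the four toxicity powers stated for 12 per arm is delivered by the one-sided Fisher exact test that the plan names: 84, 75, 64 and 82% instead of 90, 80, 80 and 90%

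*Combined protocol and SAP*

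**What the plan says.** All of this is in protocol section 6.i.n, Data analysis, under Biostatistical analysis, except the arm sizes, which are also in the Design paragraph of the Schema.

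- Test: "For SAEs, the exact Fisher test will be used".
- Sidedness: "Given this one-sided decision strategy we will further increase power by using one-sided tests".
- Design target: "Thus, we want to guarantee 90% power for the above differences at the 10% level". For toxicity, the difference meant is 50% v 5%.
- Size: "A total of 24 patients will be enrolled into one of two Arms of 12 patients each".
- Main claim: "this sample size also guarantees a 90% power to detect an increase in the cumulative incidence of SAEs from 5" per cent in the placebo group "to 50% in the vaccine group at the 10% level (or a 80% power at the 5% level").
- Second claim: "A 40% cumulative incidence could be detected with 80% power at the 10% level (or a 90% power at the 20% level").

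The section then gives one-sided exact p-values for three outcomes: .109 for 3 v 0 SAEs, .158 for 4 v 1 and .077 for 5 v 1. It derives an SAE stopping rule from them. The study stops after the third vaccine SAE if placebo has none, and after the fourth unless placebo has more than one. The section does not say how the four powers were calculated.

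**The concern.** Fisher's test is conservative in small samples because only a few p-values can occur. With 12 per arm, powers that match the round planning targets should be checked by enumeration. The plan's own p-values give reason for doubt: two of the three outcomes it lists miss the 10% level, although they are the counts on which its stopping rule acts.

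Acute toxicity is one of two primary outcomes, and the plan chose a lenient level and one-sided tests so as not to overlook it. If the named test falls short of its stated power, readers of the protocol are relying on an assurance that the specified analysis does not give.

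**Working it through.** **Inputs, all from the Biostatistical analysis section.** n = 12 per arm; one-sided test; placebo incidence 5%; vaccine incidence 50% (levels 10% and 5%) or 40% (levels 10% and 20%). Each patient counts once, as with or without an SAE, and all 12 per arm are evaluable.

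**Step 1. The plan's p-values reproduce as ordinary one-sided Fisher values.**
- 3 v 0: C(12,3)/C(24,3) = 220/2024 = .1087
- 4 v 1: [C(12,4)·12 + C(12,5)]/C(24,5) = 6732/42504 = .1584
- 5 v 1: [C(12,5)·12 + C(12,6)]/C(24,6) = 10428/134596 = .0775

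So the plan does mean the ordinary Fisher test.

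**Step 2. A formula that comes near the stated powers.** The pooled normal approximation without continuity correction is

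power = Φ{[(pV − pP) − z·√(2p̄(1 − p̄)/n)] / √([pP(1 − pP) + pV(1 − pV)]/n)}.

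- 50% v 5%, 10% level: (.45 − 1.2816 × .1823)/.1575 = 1.374, power 91.5%
- 50% v 5%, 5% level: (.45 − 1.6449 × .1823)/.1575 = 0.954, power 83.0%
- 40% v 5%, 10% level: (.35 − 1.2816 × .1705)/.1548 = 0.850, power 80.2%
- 40% v 5%, 20% level: (.35 − 0.8416 × .1705)/.1548 = 1.334, power 90.9%

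Solved for sample size, the formula returns 12 per arm in all four cases.

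**Step 3. Exact power of the named test.** For each placebo count c, find the smallest vaccine count a(c) with Fisher p at or below the level. Then power = Σ P(C = c) × P(A ≥ a(c)), with C ~ Bin(12, .05) and A ~ Bin(12, pV).

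The placebo probabilities for c = 0 to 4 are .5404, .3413, .0988, .0173 and .0021.

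| Level | a(0) | a(1) | a(2) | a(3) | a(4) |
| --- | --- | --- | --- | --- | --- |
| 5% | 4 | 6 | 7 | 8 | 9 |
| 10% | 4 | 5 | 6 | 8 | 9 |
| 20% | 3 | 4 | 5 | 7 | 8 |

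For 50% v 5% at 10%: .5404 × .9270 + .3413 × .8062 + .0988 × .6128 + .0173 × .1938 + .0021 × .0730 = .840.

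For 40% v 5% at 10%: .5404 × .7747 + .3413 × .5618 + .0988 × .3348 + .0173 × .0573 + .0021 × .0153 = .644.

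| Scenario | Stated | Normal approximation | Fisher, exact | Shortfall (points) |
| --- | --- | --- | --- | --- |
| 50% v 5%, 10% level | 90% | 91.5% | 84.0% | 6.0 |
| 50% v 5%, 5% level | 80% | 83.0% | 75.2% | 4.8 |
| 40% v 5%, 10% level | 80% | 80.2% | 64.4% | 15.6 |
| 40% v 5%, 20% level | 90% | 90.9% | 81.8% | 8.2 |

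**Step 4. The cause.** At the 10% level Fisher first rejects at 4 v 0 (p = .047), 5 v 1 (.077) and 6 v 2 (.097). The largest rejection probability over all common incidences is about 5.0%, so roughly half of the permitted 10% goes unused.

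**Step 5. Adding the SAE stopping rule.** Applied to final counts, the rule adds exactly two outcomes to the 10% rejection region, 3 v 0 and 4 v 1.
- 50% v 5%: .8401 + .5404 × (.9807 − .9270) + .3413 × (.9270 − .8062) = .910
- 40% v 5%: .6444 + .5404 × (.9166 − .7747) + .3413 × (.7747 − .5618) = .794

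**The case against.** The best defence is that the final Fisher test is not the plan's only protection. The SAE stopping rule acts at 3 v 0 and 4 v 1, the outcomes that Fisher leaves just outside its 10% region. Step 5 shows that test and rule together flag toxicity with probability 91.0% and 79.4%, close to the stated 90% and 80%. Applying the rule in sequence could only add detections. The protocol also has a separate rule on dose-limiting toxicity, not counted here because its endpoint differs. This defence stands as far as the practical consequence at the 10% level goes. It does not rescue the text, which attaches the powers to the sample size and the level of a test. Nor does it help at the 20% level, where Fisher already rejects at 3 v 0 and 4 v 1 and the power stays at 81.8%.

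Three stronger readings are tempting, and the documents do not support them.

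- A reader might infer that the trial has a 36% chance of overlooking a 40% SAE incidence (100 − 64.4 = 35.6%). That is the miss rate of the final Fisher test alone. With the stopping rule it is about 20.6%.
- A reader might state as fact that the powers came from the normal approximation. That is likely, since the formula returns 12 per arm each time, but the plan names no method and the formula gives 83.0% where the plan says 80%. Mid-p (91.4, 81.8, 79.6, 92.5%) and Barnard's test (91.4, 84.7, 79.6, 90.4%) also come close.
- A reader might say the plan ranks missed toxicity as the worst error. It does not: it applies a similar argument to activity and gives no ranking.

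It can also be said that this is a 24-patient phase I/II study and that the gap on its main toxicity target is 6 points. That bears on how grave the error is, not on whether the figures are right.

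**Conclusion.** The four toxicity powers are misstated for the test that the plan specifies. One-sided Fisher with 12 per arm gives 84.0, 75.2, 64.4 and 81.8% against 90, 80, 80 and 90%, and one of the missed figures is described as guaranteed. Two-sided Fisher is lower still (75.2, 58.8, 55.0 and 64.4%), so sidedness does not explain the gap. Rounding does not either.

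The defect is a wrong description of the final test's power. It does not show that the trial as a whole is likely to miss severe toxicity. The p-values quoted in the section are correct.

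The result assumes independent patients, one yes-or-no SAE outcome each, and 12 evaluable per arm before the cross-over. The power section makes no allowance for losses, and replacement of patients who discontinue is at the investigator's discretion; fewer evaluable patients would lower the power further. The conclusion does not depend on how the stated figures were obtained.

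**What to change.** **Needed.** Keep Fisher, restate its powers as 84, 75, 64 and 82%, name the method (exact enumeration), and replace the wording that promises a guarantee. This costs a few words and four numbers. It leaves the sample size, the quoted p-values and the stopping rule as they are. The stated target of 90% at the 10% level should then be described as not met by the toxicity test alone. For reference, Fisher would need 16 per arm to reach all four stated powers (15, 14, 16 and 15 taken singly).

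**Optional.** Pre-specify Boschloo's exact unconditional test, one-sided, in place of Fisher. With the same 24 patients its powers are 91.4, 84.0, 79.6 and 90.4%; the third is 0.4 points under the stated 80%. Its maximum size is 8.1% at the 10% level, and its 10% region begins at 3 v 0 and 4 v 1, the counts on which the stopping rule already acts. The price is a less familiar test. The three Fisher p-values in the section, from which the stopping rule is derived, would also have to be updated to match. This is a design choice; the error is corrected without it.

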#### Serious Adverse Events

All serious adverse events (defined below), whether or not deemed drug-related or expected, must be reported by the Principal Investigator or designee to the IRB within 24 hours (one working day) by telephone, and to the GCRC Clinical Research Officer. Written reports must follow as soon as possible, which include full descriptions of the event and any sequelae. The PI will report any unexpected and serious adverse event within 7 calendar days by phone or fax to the FDA, and follow within 15 calendar days by written form to the FDA. Any actions taken by the FDA or IRB will be reported by the PI to the NCI.

These stipulations includes serious adverse events that occur any time after the inclusion of the subject in the study (defined as the time when the informed consent is signed), up to 30 days after the subject completes or is discontinued from the study. The subject is considered completed after the completion of the last visit, either as documented in the Study Flow Chart of the protocol. Discontinuation is the date a subject and/or Investigator determines that the subject can no longer comply with the requirements for any further study visits or evaluations (eg the subject is prematurely discontinued from the study; see Stopping rules).

A serious adverse event in this study is defined as any event that:

Is fatal,

Is life-threatening (defined as the patient being at immediate risk of death from the AE as it occurred),

Is significantly or permanently disabling,

Requires in-patient hospitalization, or prolongs hospitalization.

Important medical events that may not fit these criteria may also be considered a serious adverse drug experience when, based upon appropriate medical judgment, they may jeopardize the patient and may require medical or surgical intervention to prevent one of the outcomes listed in this definition.

In addition to reporting serious and unexpected adverse events to the FDA, the PI will also submit in a written report any finding from tests in laboratory animals that suggests a significant risk for human subjects including reports of mutagenicity, teratogenecity, or carcinogenicity within 15 calendar days of the PI’s initial receipt of the information.

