Any severe adverse reactions (CTC Grade 3) will also be reported by the PI to the GCRC Clinical Research Officer within 48 hours. Medical intervention will be initiated as appropriate and referred for further care if necessary. The PI will not authorize further administration of the vaccine to other patients until consultation with the GCRC Clinical Research Officer and Rockefeller University’s IRB.

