### Stopping rules

#### Criteria for Subject Study Discontinuation

- Development of an exclusionary condition as outlined in section (6)i.e.2, prior to or during vaccination, with the following exceptions:
  - a course of palliative radiation treatment during the study
- platelet counts that drop > 50% from baseline.
  - hemoglobin that drops sufficiently to require transfusion.
  - if the patient develops an infection requiring treatment as an inpatient.
- Failure by the subject to attend three consecutive clinical study visits.
- Request by the subject to withdraw.
- Clinical reasons judged by the study physician to be life threatening, even if not addressed in the toxicity management of the protocol.
- Completion of week 17 or in some patients, week 29 in Arm 1.
- Completion of week 25 or in some patients week 37 in Arm 2.
- Any dose limiting toxicity. A dose limiting toxicity is defined as:
  1. any grade 2 or greater allergic toxicity or asymptomatic bronchospasm or generalized urticiaria
  2. any grade 3 or greater toxicity (hematologic or non-hematologic)
  3. any grade 2 or greater autoimmune reactions

If a subject discontinues prior to completion of the study, the reason for and date of the discontinuation will be recorded. The date of the last dose of study vaccine will also be recorded. Subjects who discontinue prior to study completion may be replaced at the discretion of the Investigator.

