Severe (Grade 3) or potentially life threatening (Grade 4) local reactions, the Rockefeller University GCRC Clinical Research Officer ([name]) must be notified within 48 hours. For grade 4 local reactions, definitive medical and/or surgical intervention should be undertaken as appropriate. Following Grade 3 or Grade 4 local reaction, further vaccines should not be given to other patients prior to consultation with the Rockefeller University GCRC Clinical Research Officer ([name]), and by the PI in conjunction with the Rockefeller Universities Institutional Review Board (IRB).

Systemic reactions

Systemic reactions will be graded according to the CTC version 3.0 (http://ctep.info.nih.gov).

All nonlocal Grade 3 or 4 reactions (for example, elevated temperature following immunization) thought definitely, possibly or probably related to vaccination, will be reported within 48 hours to the Rockefeller University GCRC Clinical Research Officer ([name]). Further vaccines should not be given to other patients prior to consultation with the Rockefeller University GCRC Clinical Research Officer ([name]), and by the PI in conjunction with the Rockefeller Universities Institutional Review Board (IRB).

The study will be stopped if 1 of 3, 2 of 6, 3 of 9, or 4 of 12 subjects experience dose limiting toxicity as defined under 6.i.m. Stopping rules, 1) Criteria for Subject Study Discontinuation. This applies to subjects in both Arm 1 and 2 while he is receiving the investigational product.

If a patient is injected with a DC-vaccine prior to knowing that a contaminant was present (e.g. prior to a 14-day culture becoming positive), the patient will be immediately contacted and undergo a complete history and physical examination. Blood cultures and appropriate laboratory tests will be drawn.

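### The placebo-controlled SAE stopping rule has no trigger after the fourth vaccine SAE, so once two or more placebo SAEs come first it cannot fire, even on evidence stronger than that at which it stops

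*Combined protocol and SAP*

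**What the plan says.** The rule closes the toxicity part of Biostatistical analysis. It has two triggers. The first stops the study at the third vaccine SAE if the placebo group has had none. The second is the last: "After the fourth SAE in the vaccine group, the study is stopped unless more than one SAE has already occurred in the placebo group". It rests on one-sided exact Fisher p-values at 12 per arm: .109 for 3 v 0 and, with one placebo event, "four and five severe adverse events in the vaccine group yield a p-value of .158 and .077, respectively". The working level comes from the same section: "Thus, we want to guarantee 90% power for the above differences at the 10% level", one-sided, with a target to "detect a 50% incidence of severe adverse events (acute toxicity) vs. a 5% incidence".

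A second rule, under Vaccine Toxicity, ignores the placebo count: "The study will be stopped if 1 of 3, 2 of 6, 3 of 9, or 4 of 12 subjects experience dose limiting toxicity". Criteria for Subject Study Discontinuation defines a DLT as "any grade 3 or greater toxicity (hematologic or non-hematologic", or a grade 2 or greater allergic or autoimmune reaction.

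The meaning of SAE is not fixed. Serious Adverse Events gives the usual seriousness definition, which includes in-patient hospitalisation at any grade. Biostatistical analysis also calls the same counts severe events, and Serious Adverse Events ties severe to grade 3: "Any severe adverse reactions (CTC Grade 3) will also be reported by the PI".

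**The concern.** Placebo counts cannot fall. Once the fourth vaccine SAE has passed with two or more placebo SAEs already recorded, and at least one of those came before the third vaccine SAE, nothing later can trigger this rule. It would stop at 3 v 0 but stay silent at 8 v 3, which is the stronger evidence. It is the only stopping rule that uses the placebo arm, and Broad Objectives says that arm is there to help judge whether events are treatment related. What is at stake is a predefined early stop in a trial where every Arm 2 man later crosses over to vaccine.

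**Working it through.** **Inputs.** From the plan: 12 per arm, one-sided Fisher exact test, 10% level, rates of 50% (vaccine) and 5% (placebo). Assumed: backgrounds of 10% and 20%, at most one SAE per man, and all orders of events equally likely.

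**1. The plan's own p-values.** With x vaccine and y placebo patients affected, p = sum over k >= x of C(12,k)·C(12,x+y−k) / C(24,x+y).
- 3 v 0: 220/2,024 = .109
- 4 v 1: (5,940 + 792)/42,504 = .158
- 5 v 1: (9,504 + 924)/134,596 = .077

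All three match.

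**2. Where the rule lapses.** 3 v 1 gives 3,135/10,626 = .295, and 4 v 2 gives 43,098/134,596 = .320. Not stopping at those points is right.

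**3. Later crossings of the 10% level.**
- 6 v 2: (60,984 + 9,504 + 495)/735,471 = .097 (5 v 2 is .185)
- 8 v 3: 124,224/2,496,144 = .050 (7 v 3 is .107)
- 9 v 4 .050; 10 v 5 .045; 10 v 6 .097; 11 v 7 .078; 12 v 8 .047
- With nine placebo patients affected the level cannot be met (12 v 9 is .109).

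**4. How often the rule lapses.** For x >= 4 and y >= 2 there are C(x+y,y) orders. The rule fires at the third vaccine SAE in C(x+y−3,y) of them, and at the fourth in 3·C(x+y−5,y−1). The lapse share is

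L(x,y) = 1 − [C(x+y−3,y) + 3·C(x+y−5,y−1)] / C(x+y,y).

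For 6 v 2 this is 1 − (10 + 9)/28 = .321. Weighting L by the two binomial distributions, with a 50% vaccine rate and the DLT rule ignored:

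| Placebo rate | Rule lapses | Unstopped, final p <= .10 | Rule's stopping chance now | With the counts in step 3 |
|---|---|---|---|---|
| 5% (plan) | 4.1% | 1.7% | 92.0% | 93.8% |
| 10% (assumed) | 13.1% | 4.3% | 81.7% | 86.6% |
| 20% (assumed) | 34.4% | 6.6% | 59.1% | 67.9% |

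At the plan's rates, 92% of the 1.7% has exactly two placebo SAEs, so 6 v 2 and above is the case that matters. The counts for four or more placebo patients add almost nothing.

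**5. Overlap with the DLT rule.** I simulated 400,000 trials per setting, with looks at 3, 6, 9 and 12 Arm 1 men in random order and DLTs only among men with an SAE. The unstopped share depends on the assumed fraction of those men who also have a DLT:

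| Fraction with a DLT | 5% placebo | 10% | 20% |
|---|---|---|---|
| A quarter | 0.9% | 2.4% | 3.6% |
| A half | 0.4% | 0.9% | 1.2% |
| All | 0 | 0 | 0 |

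**The case against.** The strongest reply is that the gap may not exist. Biostatistical analysis states its target as severe events, severe is tied to grade 3, any grade 3 toxicity is a DLT, and four DLTs in 12 men stop the study whatever the placebo count. If SAE means grade 3+ and toxicity carries no attribution filter, that argument is complete and the gap is nil. The plan does not settle the reading. Under the seriousness definition, a hospitalisation below grade 3 is an SAE but not a DLT, and Monitoring and follow-up allows admission at the PI's discretion. An event judged unrelated may also escape the DLT rule if toxicity is read as in the toxicity endpoint, which requires at least possible relation. A 6 v 2 table can hold up to three DLT men, so the gap needs several non-DLT events, not only non-DLT events.

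Other safeguards stand too. Serious events, "whether or not deemed drug-related or expected, must be reported by the Principal Investigator or designee to the IRB within 24 hours". After grade 3 or 4 local reactions, and systemic ones thought related, vaccination of other patients is held pending consultation with the Clinical Research Officer and the IRB. Safety is analysed after each immunization, and the monitoring team meets monthly. DLTs that are not SAEs (grade 2 allergic or autoimmune reactions) would lower the residual further. If 10% of the other men had one (an assumption), the 5%-background figures would fall to about 0.75% (a quarter with DLTs) and 0.25% (a half).

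A reader might infer that two placebo SAEs leave the trial with no safety stop, or that the rule is wrong to continue at 4 v 2. The documents support neither: the DLT rule still runs, and p = .320 at 4 v 2 is no ground for stopping.

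**Conclusion.** The point holds as a minor incompleteness. The placebo-controlled rule stops on weaker evidence than some later tables at which it can no longer fire. The gap matters only where enough vaccine SAEs are not DLTs for the DLT rule not to stop the study first. Its size at the plan's rates is 1.7% of trials if the DLT rule is ignored, and about 1% or less once a quarter or more of the men with SAEs also have DLTs. It grows with background rates that the plan does not assume. These figures rest on 12 evaluable men per arm, one SAE per man, random event order, and the DLT looks applied to the 12 Arm 1 men. Nothing is lost from the final analysis: the Fisher test would still show 6 v 2 or 8 v 3. Only a predefined early stop is missing. The undefined SAE and the counting unit need repair on any reading, because the triggers count events while the quoted p-values hold for patients.

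**What to change.** In Biostatistical analysis:

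1. State whether SAE means serious, as defined under Serious Adverse Events, or severe (grade 3+).
2. In every trigger, count patients with at least one SAE before the cross-over.
3. Add: *With 2, 3, 4, 5, 6, 7 or 8 placebo patients with an SAE, the study is stopped at the 6th, 8th, 9th, 10th, 10th, 11th or 12th vaccine patient with an SAE.*
4. State that the study stops when either this rule or the DLT rule is met, and cross-refer from Vaccine Toxicity.

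Use fixed counts based on the planned 12 per arm, like the existing triggers, and no separate p <= .10 clause. During accrual the two would disagree: 7 v 3 is .107 at 12 per arm but .089 at 10. If SAE is defined as severe and every such event is a DLT, items 1, 2 and 4 are enough.

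The cost is a definition, a counting unit, two sentences and a cross-reference. The downside is slightly more early stopping when both arms share a high SAE rate: +0.2 points at 20% (14.2% to 14.4%), +1.2 at 30% (18.2% to 19.4%) and +2.7 at 40% (19.1% to 21.8%). At 5% and 10% the rise is below 0.01 points.
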